## Abstract

**Abstract:**

**Background:**

Migrants and refugees with low language proficiency (LLP) in the dominant language of their host country have a higher risk of suffering from certain mental health disorders compared with non-migrant populations. They are also more likely to experience a lack of access to mental healthcare due to language-related and culture-related barriers. As part of the MentalHealth4All project, a digital multilingual communication and information platform was developed to promote access to mental healthcare for LLP migrants and refugees across Europe. This paper describes the study protocol for evaluating the platform in practice, among both health and/or social care providers (HSCPs) and LLP migrants and refugees.

**Methods and analysis:**

We will conduct a pretest–post-test cross-national survey study to evaluate the platform’s effect evaluation (primary objective) and process evaluation (secondary objective). The primary outcomes (measured at T0, T2 and T3) are four dimensions of access to mental healthcare services: availability, approachability, acceptability and appropriateness of mental healthcare. Secondary outcomes (measured at T2) are: actual usage of the platform (ie, tracking data), perceived ease of use, usefulness of content, comprehensibility of information, attractiveness of content and emotional support. Participants will be recruited from nine European countries: Belgium, Germany, Italy, Lithuania, the Netherlands, Poland, Slovakia, Spain and the UK. Using convenience sampling through professional networks/organisations and key figures, we aim to include at least 52 HSCPs (ie, 6–10 per country) and 260 LLP migrants (ie, 30–35 per country). After completing a pretest questionnaire (T0), participants will be requested to use the platform, and HSCPs will participate in an additional personalised training (T1). Next, participants will fill out a post-test questionnaire (T2) and will be requested to participate in a second post-test questionnaire (T3, about 6–8 weeks after T2) to answer additional questions on their experiences through a brief phone interview (T3 is optional for migrants/refugees).

**Ethics and dissemination:**

For all nine countries, the ethical review board of the participating university (hospital) has assessed and approved the protocol. If successful, the MentalHealth4All platform will be made publicly available to help improve access to mental healthcare services, as well as HSCPs’ cultural competencies in delivering such services, for any LLP migrants and refugees across Europe (and beyond). Findings will also be disseminated through peer-reviewed journals and conferences.

**Registration details:**

The ‘MHealth4All project’ was prospectively registered on Open Science Framework, DOI: 10.17605/OSF.IO/U4XSM.

STRENGTHS AND LIMITATIONS OF THIS STUDYThe broad geographical and linguistic coverage of the MentalHealth4All consortium ensures recruitment of diverse groups of low language proficiency (LLP) migrants and refugees and health and/or social care providers (HSCPs).The complementary skills, expertise and experiences of the consortium partners in working and collaborating with LLP migrants and refugees enable us to draw on existing collaborations for data collection.Although this study’s main challenge concerns the recruitment/drop-out of LLP migrants and refugees, previous studies in the project have proven the feasibility of including these populations in our research.To ensure implementation in practice, HSCPs follow a webinar and personalised training session in which they learn how to (overcome barriers to) integrate the platform in their daily practice.The appropriateness of performing sensitivity analyses with only migrants who experience mental health issues and of exploring differences across countries depends on the final sample.

## Introduction

 Mental health is a vital part of one’s well-being.^1^,^3^ Yet, about one billion people worldwide suffer from (diagnosable) mental health disorders.^1 4^ Migrants and refugees are at increased risk of suffering from specific disorders such as post-traumatic stress, depression and psychosis-related disorder, with higher prevalence rates compared with those of non-migrant populations.^5^,^9^ Yet, migrants’ and refugees’ access to mental healthcare services is often severely hindered,^10^,^16^ because of a combination of cultural barriers such as mental health stigma and taboo, and structural barriers such as low language proficiency (LLP) in the dominant language(s) of their country of residence, a lack of information about the healthcare system in one’s mother tongue and (perceived) discrimination.^10 11 17 18^ Language barriers between clients and their health and/or social care providers (HSCPs) who do not share a common language form one of the main factors contributing to persisting health inequalities in access to (mental) healthcare.^19^ Notwithstanding international human rights standards to reduce health inequalities,^20^ the European Commission has called for more attention to integration measures for refugees and migrants in Europe, in particular concerning access to (mental) healthcare services.^21^

With the number of migrants and refugees at unprecedented and still increasing levels worldwide,^22 23^ responding to the call made by the European Commission and promoting their access to mental healthcare is of crucial importance. To achieve this, digital or technology-based interventions could provide a necessary partial solution.^11 24 25^ Digital interventions have several advantages over non-digital interventions, among which wider access to expert care and the possibility to use various modalities suited to different literacy levels.^26^ Previous studies have shown that—particularly cocreated^27^—(digital) interventions have successfully enhanced healthcare access and health outcomes in marginalised populations.^28^,^31^ Building on these successes, our platform is designed to address the unique challenges faced by LLP refugees and migrants who suffer from mental health problems. Specifically in the context of promoting access to mental healthcare for LLP migrants and refugees, digital interventions could build on recommendations from previous studies by offering culturally sensitive multilingual materials,^32^ including all stakeholders in a co-creation process^33^ and also offering support to providers who refer to and/or offer mental health services.^34^

Despite their great potential, evidence-based digital interventions to promote access to mental healthcare services for these target groups across Europe are still very scarce and often not properly evaluated in terms of their effectiveness.^35^ The MentalHealth4All project aims to fill these gaps by designing and evaluating a culture-sensitive multilingual digital platform to promote this access, which is defined as ‘the *opportunity* to use health services, reflecting an understanding that there is a set of circumstances that allows for the use of appropriate health services’.^36^ This evaluation study will primarily focus on four dimensions of access, namely: availability (ie, the presence and capacity of facilities), approachability (ie, access to information on (patient) rights, services available and costs of services), acceptability (ie, cultural competence by providers) and appropriateness (ie, how well the services provided match the needs of the refugee/migrant populations).^37 38^ Building on insights from previous parts of the project^14 39 40^ and following the Spiral Technology Action Research (STAR) Model,^41^ an evidence-based sustainable digital information and communication platform was cocreated with LLP migrants and refugees in order to promote their access to mental healthcare on these four dimensions.

This study protocol describes the final part of the MentalHealth4All project, which aims to prospectively evaluate the intervention in practice across nine European countries. The primary objective of this study is the effect evaluation, that is, to evaluate the effects of the digital platform on the main dimensions of perceived access to mental healthcare services.^37 38^ The secondary objective of this study is the process evaluation, that is, to evaluate the digital platform with regard to the process of implementing the platform in healthcare practice. Corresponding with these objectives, we will answer the following research questions:

*RQ1*. How does the digital platform affect participants’ (ie, migrants/refugees and HSCPs) perceptions of access to mental healthcare in terms of: (1) availability, (2) approachability, (3) acceptability and (4) appropriateness?

*RQ2*. How do participants (ie, migrants/refugees and HSCPs) use the digital platform in terms of the pages/videos they access and average duration of engagement?

*RQ3*. How do participants (ie, migrants/refugees and HSCPs) evaluate the digital platform in terms of: (1) ease of use, (2) usefulness of the content, (3) comprehensibility of the information, (4) attractiveness of content and (5) emotional support?

## Methods and analysis

### Study design

To answer the research questions, a pretest–post-test cross-national study will be conducted to evaluate the MentalHealth4All digital platform in nine European countries (ie, Belgium, Germany, Italy, Lithuania, the Netherlands, Poland, Slovakia, Spain or the UK). These countries were selected as consortium partners to ensure broad geopolitical representation across northern, eastern, southern and western Europe. Due to the nature of the study design and intervention, either randomising or blinding participants is not possible. We will apply an intention-to-treat approach,^42 43^ that is, including participants regardless of how long they have used the digital platform. This approach aligns well with actual practice where, for instance, some people may search for specific information and therefore briefly use a specific part of the platform, while others may go through the entire platform to explore what possibilities there are. For each country, the ethical review board of the participating university/hospital has assessed and approved the protocol.

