After agreeing to participate, participants will receive the link to the questionnaires (see online supplemental appendix 1) and a personalised log-in code (for both the questionnaires and the platform). Participants will then be asked to go through three different steps, as illustrated in figure 1. First, participants will be asked to fill out the pretest questionnaire to establish a baseline, which starts by asking informed consent (T0). Second, they will be asked to use the multilingual digital platform/intervention (T1; ie, for HSCP participants, this also includes participation in personalised training). Third, participants will be asked to fill out the post-test questionnaire to evaluate the platform’s effects on the four dimensions of access to mental healthcare immediately after having used the platform (T2). Fourth, after about 6–8 weeks after T1, HSCPs will participate in a brief phone or online interview to answer some final questions on their usage of/experiences with the digital platform and its effects on access to mental healthcare (T3). The digital platform and the questionnaires will be available online in multiple languages in order to match participants’ mother tongue or a possible second language. If a participant prefers, the surveys could be administered on paper or verbally, for instance, by a (multilingual) research assistant or with the possible help of an interpreter.

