#### Primary outcome measurements

In line with RQ1, the main study parameter is access to mental healthcare services, measured by means of four dimensions, that is, availability, approachability, acceptability and appropriateness.^37 38^ These four dimensions are the main endpoints for this study. Based on other existing questionnaires, we selected and/or developed our own questions to assess these dimensions. In particular, we used existing scales for mental health literacy,^45^,^47^ and the Canadian Community Health Survey on accessibility, acceptability and availability^48^ as inspiration for these endpoints. Additionally, we supplemented the dimensions with statements that were considered of particular relevance in the current context (ie, migrants/refugees and mental health) based on the extensive expertise of the project team. These primary outcome measurements will be assessed at T0 (pre test), T2 (first post test) and T3 (second post test).

*Availability of care*: the presence and capacity of facilities will be assessed with five items on a five-point Likert scale (1=strongly disagree, 5=strongly agree).*Approachability of care*: this dimension entails access to information on (patient) rights, services available and costs of services and will be assessed with seven items on a five-point Likert scale (1=strongly disagree, 5=strongly agree).*Acceptability of care*: this dimension assesses providers’ cultural competence and will be assessed with four items on a five-point Likert scale (1=strongly disagree, 5=strongly agree).*Appropriateness of care*: this dimension indicates how well the services provided match the needs of the refugee/migrant populations and will be assessed with six items on a five-point Likert scale (1=strongly disagree, 5=strongly agree).

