### Statistical analysis

The latest version of IBM SPSS Statistics will be used to statistically analyse the data. The data analysis will be performed by researchers from the project lead of this work package, that is, the University of Amsterdam. For the analysis of the primary endpoints, that is, the four dimensions of access to mental healthcare, we will perform one-sided t-tests and repeated measure ANOVAs to evaluate differences in the measurements between the pre test (baseline survey) and post tests per group of participants (ie, migrants/refugees and HSCPs separately). Additionally, we will perform ANOVAs to check for possible covariates. If possible, we will perform sensitivity analyses with only the migrants/refugees who are currently experiencing self-reported mental health issues and explore differences between the participating countries. We will use a significance level of p≤0.05 for all analyses. Descriptive statistics will be provided for the secondary endpoints. Additionally, descriptive statistics and frequency distributions will also be generated for the participants’ sociodemographics.

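### The analysis is labelled intention-to-treat, but the timing of T2 and the named tests give an estimate among platform users who returned the post-test

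*Protocol article*

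**What the plan says.** Four parts of the protocol article bear on who is analysed.

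- **Study design** states the principle, "We will apply an intention-to-treat approach", and explains it as "including participants regardless of how long they have used the digital platform". The reasoning given there contrasts brief with thorough use. Non-use is not mentioned.
- **Procedures** places the first post-test "immediately after having used the platform (T2"). It describes no T2 for an enrolled participant who never uses the platform. For T3 it names only providers: "HSCPs will participate in a brief phone or online interview".
- **Primary outcome measurements** sets three time points for the four access dimensions: "These primary outcome measurements will be assessed at T0 (pre test), T2 (first post test) and T3 (second post test"). The abstract adds that "T3 is optional for migrants/refugees".
- **Statistical analysis** names the methods for these endpoints: "we will perform one-sided t-tests and repeated measure ANOVAs to evaluate differences in the measurements", comparing the pre-test with the post-tests separately for migrants/refugees and providers.

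The strengths and limitations box names recruitment and dropout of migrants as the study's chief difficulty. The only response shown is an allowance in the per-country recruitment targets under Sample size calculation.

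**The concern.** A reader who sees the intention-to-treat label will take the result to cover everyone enrolled. The procedure and tests point to a narrower set: people who used the platform and then answered the post-test.

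This matters more than usual because the study has one arm. The within-person change is the whole effect estimate, and no comparison group would show that less engaged people had gone missing. Those who never log in, or who stop because the platform does not help them, are plausibly the ones without T2. The result also has consequences, since the Intervention section makes open release of the platform depend on favourable findings.

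A second loss concerns T3. If it enters a repeated-measures ANOVA, migrants who decline an optional interview lose their valid T0 and T2 answers as well.

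**Working it through.** **1. The plan's own figure.** Sample size calculation gives n=52 from effect size 0.2, alpha 0.05, power 0.80, 2 groups and 2 measurements. The within-person correlation is not stated, so ρ=0.5 is assumed. The effect size is printed as f2, but 52 follows from f=0.2.

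- λ = f²·N·m/(1−ρ) = 0.04 × 52 × 2 / 0.5 = 8.32, with df 1 and 50.
- Power is 0.807 at N=52 and 0.791 at N=50, so 52 is reproduced.

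This calculation assumes 52 people with both measurements, so it is already a number of completers.

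**2. Who enters each analysis as normally run.**

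| Participant has | T0–T2 paired t-test | ANOVA with T0, T2 and T3 |
|---|---|---|
| T0 only (for example, never used the platform) | out | out |
| T0 and T2, declined T3 | in | out |
| T0, T2 and T3 | in | in |

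The t-tests are read as paired because they compare pre-test with post-test within each group. No row keeps a participant who has T0 only. The optional T3 affects only the right-hand column and any T0–T3 contrast. No T3 uptake is stated, so no count of lost migrants can be given.

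**3. Effect on the estimate.** Let d be the proportion with T0 but no T2, Δ the mean change in completers and δ the mean change in the rest.

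- All-enrolled change = (1−d)Δ + dδ.
- Bias of the completers' figure = Δ − [(1−d)Δ + dδ] = d(Δ−δ).
- With δ=0, the ratio of completers' to all-enrolled change is 1/(1−d).

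For scale, the planned effect in SD units of change is 2f/√(2(1−ρ)) = 0.4/1 = 0.40. The values of d are assumed, because the article gives none:

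| d | All-enrolled change, if completers change by 0.40 and the rest by 0 | Overstatement |
|---|---|---|
| 10% | 0.36 | 11% |
| 20% | 0.32 | 25% |
| 30% | 0.28 | 43% |

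**4. Would over-recruitment help?** It helps power but does not remove bias. Complete-case power (f=0.2, ρ=0.5, one group):

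- 260 migrants: above 0.99 with 182 left (30% loss), and 0.94 with 78 left (70% loss).
- 52 providers: 0.77 with 47 left (10% loss), and 0.72 with 42 left (20% loss). The per-country range of 6–10 gives 54 to 90 providers over nine countries. With 90 enrolled, power is 0.92 after 20% loss.

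For migrants the issue is therefore who is represented, not power.

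**5. Would a mixed model alone be enough?** No. A non-user supplies only T0. Under missing at random, the model in effect predicts that person's T2 from the completers' relation between T0 and T2. In the scenario of step 3 it would still return roughly the completers' change. It does recover T0 and T2 data from migrants without T3.

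**The case against.** The strongest reply is that Study design says what it means by the label, namely any duration of use, and sets no minimum-use threshold. Among users who return T2, the procedure meets that rule. With no randomisation there is also no randomised comparison to protect. This stands, and it narrows the point to zero-use participants and those without a post-test. The label will still be read as covering everyone enrolled.

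Several stronger readings are tempting, but the article does not support them:

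- *Both named tests lose every migrant who skips T3.* The T0–T2 t-test keeps them.
- *A three-time-point ANOVA is certain and would discard most migrants.* The wording on post-tests, together with T3 as a primary time point, makes such a model likely but does not fix it. Sample size calculation uses two measurements, and T3 uptake is not given.
- *Non-users are barred from T2.* Procedures gives the questionnaire link together with the log-in code once a person agrees to take part. T2 is sequenced after use, but nothing says it is locked.
- *The effect is overestimated.* The direction depends on Δ−δ, which is unknown.
- *No missing-data method exists.* A separate analysis plan could specify imputation, and silence in a condensed article is not a fault. The point rests on the mismatch between the stated label and the stated timing and tests. An analysis plan could not recover T2 answers that were never requested.

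Sending T2 to everyone at a fixed interval is also open to debate. It would give up the measurement taken right after use, and much of T2 asks for opinions on the platform that a non-user cannot give.

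**Conclusion.** The concern holds in this limited form. As written, the plan yields an estimate among users who returned the post-test, under a label that suggests all enrolled. Any ANOVA that includes T3 would further delete usable T0 and T2 data from migrants who decline it.

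The size of any bias is unknown. The 11%, 25% and 43% figures rest on two assumptions that are not in the article: the loss rates of 10%, 20% and 30%, and no change in people without T2. If those people changed as much as completers, there would be no bias; if they changed more, the completers' figure would be too small. The statement about who is excluded assumes that the tests are run in the usual way, on complete cases.

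**What to change.** 1. For each participant group, replace the repeated-measures ANOVA with a linear mixed model on all available T0, T2 and T3 data, with time as a categorical factor. Make T2 minus T0 the primary contrast and treat T3 in migrants as secondary.
2. Add a sensitivity analysis that sets change to zero for everyone with T0 but no T2. It is needed because the mixed model assumes data missing at random and does not correct for non-users.
3. Where feasible, ask T0 completers who did not log in for the access items of T2 only. Where this is not feasible, drop the intention-to-treat label and report the result as an estimate among users who returned the post-test.

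Cost: items 1 and 2 need a little more analysis work, and SPSS can fit the mixed model. Item 3 touches data collection in nine countries, which is why relabelling is offered as the alternative. The sensitivity analysis will probably show a smaller change than the completers' figure.

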### Study population

For this study, we aim to include two main groups of participants: (1) LLP migrants and refugees and (2) HSCPs who have experience in providing (mental) healthcare for LLP migrants and refugees.

#### Inclusion criteria

The following inclusion criteria will be adhered to for migrants and refugees:

Currently living in one of the consortium’s participating countries (ie, Belgium, Germany, Italy, Lithuania, the Netherlands, Poland, Slovakia, Spain or the UK).Refugee/migrant background originating outside the country of residence.≥18 years old.Limited proficiency in the dominant language(s) of the country of residence (and therefore experiencing language barriers) as verified with a self-reported scale in the questionnaire.Sufficiently proficient to understand (at least) 1 of the 15 languages of the multilingual digital platform (ie, Arabic, Chinese, Dutch, English, French, German, Italian, Lithuanian, Persian, Polish, Russian, Slovak, Spanish, Turkish and Ukrainian).

For inclusion of the HSCPs, the following inclusion criteria will be used:

Experience in delivering (mental) healthcare to migrants and refugees (ie, at least one consultation with an LLP refugee/migrant client per month on average in the past 6 months).Currently working in one of the participating European countries (ie, Belgium, Germany, Italy, Lithuania, the Netherlands, Poland, Slovakia, Spain or the UK).Sufficiently proficient to understand (at least) 1 of the 15 languages of the multilingual digital platform.

